### 2.12. Patient and Public Involvement

Participants (children, primary caregivers, teachers, school principals, local health and education officials) in this study will participate in interviews and focus group discussions at the time of the improvement intervention program. They are not involved in the formulation of idea development, research questions, trial design, outcome measures, recruitment or study execution, data collection and analysis and interpretation of the results. In addition, they will be invited to participate in conferences to disseminate research findings to other public schools after they have been translated into Chinese.

## 3. Discussion

Although some intervention studies have been conducted in China to improve FV intake and MVPA in children, there are still gaps in the mix of interventions and in the sustainability of interventions. This should be the first cluster randomized controlled trial of school gardening, cooking activities, and sports participation in children in China. By establishing a sustainable and structured intervention program to validate its effectiveness and sustainability in improving children’s FV intake and MVPA deficits, evidence will be provided to the education sector and policy makers for the national replication of this program. 

There are several strengths of this study. First, it will be the first cluster randomized controlled trial using a combined gardening, cooking, and sports participation intervention in China. Second, the implementation of the intervention involves not only students but also primary caregivers and teachers to increase the potential for sustainability. Third, this study will assess changes in outcomes using both self-reported and objective measures, with more rigorous results. Fourth, the study will develop a process evaluation plan for the implementation of the intervention and conduct a six-month follow-up to determine the sustainability of the effect. However, limitations of the study should be considered. First, the duration and outcomes of this study is limited and more funding will be applied to implement long-term interventions in the future. Second, FV intake were measured by self-report, which is easily affected by social recognition bias, so they may not accurately represent the changes in dietary intake, studies should consider the use of serum carotenoids as dietary biomarkers in the future.

In order to ensure the sustainability of SGC and SP interventions, there are a few things which should be considered carefully. The first thing to do is to maintain the garden, kitchen and sports facilities; it is recommended that the school set up a committee including school administrators, teachers, parents, and students to work out a plan to ensure that the garden is watered and weeded, the kitchen and sports facilities is maintained on a rotating basis during weekends (and during the summer and winter holidays). Secondly, the project leader and members of the team will train interested school teachers and staff on the topic, teaching them how to teach SGC and SP and integrate them into the existing school curriculum. Finally, outreach work could be carried out in conjunction with the local education authorities, for example by producing a web-based resource containing a syllabus for SGC and SP, implementation guidelines and teaching videos for use by other schools.

## 4. Conclusions

The intake of FV and the increase of MVPA play an important role in the development of healthy habits and normal BMI for children, however, inadequate intake of FV and insufficient MVPA in children still exist in many countries. This study intends to use a cluster randomized controlled trial to explore the effects of SGC and MVPA on the fruit and vegetable intake and MVPA of Chinese children, and provide new ideas for researchers to tackle problems such as overweight and obesity in children in the future.

## Figures and Tables

**Figure 1 ijerph-19-14096-f001:**
[figure not shown]
Study flow chart.

**Figure 2 ijerph-19-14096-f002:**
[figure not shown]
Intervention in the development process.

**Table 1 ijerph-19-14096-t001:** School gardening and cooking and sport participation intervention components.

Intervention	Intervention Components	Target	Descriptions of the Content, Frequency and Duration	Person Responsible
School Gardening & Cooking	SGC Training	Teachers	Content: SGC intervention introduction; the specific operation method of each intervention process; the teacher version of the intervention process diary and partial data collection. Frequency: Only once before the intervention. Time: 1–2 h.	Project team leader and members
	Gardening Practice Intervention	Students	Content: Planting 16 seasonal vegetables and fruits in the school garden. Among the vegetables are peppers, cucumbers, beans, aubergines, red amaranth, hollow cabbage, perilla, spinach, oleander, cabbage, string beans and lettuce. Fruits include strawberries, thumb watermelon, melon and cherry tomatoes Frequency: one intervention every one to two weeks, ten times in the last semester, and six times in the next semester. Time: Each intervention lasts for 45 min.	Teachers, volunteers, and project team members
	Gardening and Nutrition Theory Intervention	Students	Content: A total of 16 gardening theory courses, including the needs of plant growth, human body growth, the importance of vegetables and fruits, 24 four solar terms and planting, etc. Frequency: one intervention every two weeks, eight times in the last semester, and eight times in the next semester. Time: Each intervention lasts for 45 min.	Teachers, volunteers, and project team members
	Cooking Intervention	Students, Primary caregivers	Content: eight seasonal vegetable and fruit salad cooking demonstration and tasting, and share the eight vegetable and fruit recipes. Frequency: One intervention every four weeks, four times in the last semester, and four times in the next semester. Time: Each intervention lasts for 45 min.	Teachers, volunteers, and project team members
	Home Gardening Intervention	Students, Primary caregivers	Content: Students grow fruits and vegetables with their parents in simple containers at home, and share gardening and nutrition theories with their parents. Frequency: no requirement. Time: No requirement.	Teachers
	Student Diary	Students	Content: Students should take the initiative to write a small diary of about 300 words after completing the activities related to gardening practice, gardening and nutrition theory knowledge learning, and salad tasting. Frequency: Writing is required after each intervention. Time: No requirement.	Teachers
	SGC Toolkit	Teachers, Volunteers	Content: Materials, tools, and textbooks.	Teachers
Sports Participation	SP Training	Teachers	Content: SP intervention introduction; the specific operation method of each intervention process; the teacher version of the intervention process diary and some data collection. Frequency: Only once before the intervention. Time: 1–2 h.	Project team leader and members
	Sports skills performance	Students	Content: Show some interesting jumping methods of pattern rope skipping, and organize students to participate in group games. Frequency: Only once before the intervention. Time: 1 h.	Members of the project team
	Exercise Skills Practice Intervention	Students	Content: Learn 24 kinds of pattern rope skipping movements, including individual patterns, double cooperation and multi-person fun rope skipping. Frequency: one intervention every two weeks, eight times in the last semester, and eight times in the next semester. Time: Each intervention lasts for 45 min.	Teachers, volunteers, and project team members
	Exercise Health Theory Intervention	Students, Primary caregivers	Content: Learn an overview of different sports, the benefits of sports, and learn how to deal with sports injuries. Frequency: one intervention every two weeks, eight times in the last semester, and eight times in the next semester. Time: Each intervention lasts for 45 min.	Teachers, volunteers, and project team members
	Sports Competitions	Students	Content: Arrange eight synchronized rope skipping competitions. Students can choose to participate in different forms of competitions according to their wishes. Frequency: One intervention every four weeks, four times in the last semester, and four times in the next semester. Time: Each intervention lasts for 45 min.	Teachers, volunteers, and project team members
	SP Toolkit	Teachers, Volunteers	Content: Materials, tools, teaching materials, certificates.	Teachers

**Table 2 ijerph-19-14096-t002:** Outcome measurements for the study.

Outcomes	Time			Equipment (Model Number, Manufacturer)	Method
	Baseline	6 Months after Baseline	12 Months after Baseline		
**Anthropometric measures**					
Height	√	√	√	GMCS-I (Xindong Huateng)	Measured to the nearest 0.1 cm at least twice
Weight	√	√	√	RGT-140 (Weighing)	Measured to the nearest 0.1 kg at least twice
Waistline	√	√	√	Tape (MyoTape)	Measured to the nearest 0.1 cm at least twice
Step number	√	√	√	Huawei Band 6 (Huawei, validity (R = 0.72) and reliability (intraclass correlation coefficient = 0.71)	Wear for one week to calculate the average
Calorie expenditure	√	√	√	Huawei Band 6 (Huawei, validity (R = 0.67) and reliability (intraclass correlation coefficient = 0.86)	Wear for one week to calculate the average
Daily minutes of MVPA	√	√	√	Huawei Band 6 (Huawei, validity (R = 0.65) and reliability (intraclass correlation coefficient = 0.76)	Wear for one week to calculate the average
Daily sleep time	√	√	√	Huawei Band 6 (Huawei, validity (R = 0.85) and reliability (intraclass correlation coefficient = 0.91)	Wear for one week to calculate the average
Daily sedentary time	√	√	√	Huawei Band 6 (Huawei, validity (R = 0.74) and reliability (intraclass correlation coefficient = 0.82)	Wear for one week to calculate the average
**PA and other behavioral conditions**					
PA frequency and attitudes of children.	√	√		6 to 17-year-old Chinese children physical activity questionnaire, CCPAQ (The CCPAQ is a valid (R = 0.78) and trustworthy (intraclass correlation coefficient = 0.70) device for measuring PA)	Students should finish the questionnaires in the classroom in the presence of the trained outcome assessors, who can provide guidance and help.
Daily Screen time	√	√		6 to 17-year-old Chinese children physical activity questionnaire, CCPAQ (The CCPAQ is a valid (R = 0.78) and trustworthy (intraclass correlation coefficient = 0.70) device for measuring PA)	Students should finish the questionnaires in the classroom in the presence of the trained outcome assessors, who can provide guidance and help.
**Dietary behavior**					
Daily intake of FV and food intake frequency	√	√		The Food Frequency Questionnaires, FFQ required for the study was developed using the food frequency questionnaire compiled by the 2016 Chinese Resident Dietary Survey with appropriate adjustments according to the study content and purposes of the study, with Cronbach’s > 0.7.	The questionnaires should be self-reported by parents or other primary caregivers of the students.
Children’s FV preferences, identification and the attitude and willingness to eat FV	√	√		Using the Dutch Eating Behavior Questionnaire child-version, DEBQ-C.Zhao Yan et al.developed the Chinese version of the children’s dietary behavior scale according to the English version of DEBQ-C, with Cronbach’s > 0.7	Students should finish the questionnaires in the classroom in the presence of the trained outcome assessors, who can provide guidance and help.
Parental attitudes towards children’s FV intake and SP	√	√		The questionnaire will be adapted from the nutrition knowledge, attitude and praxis questionnaire (KAP) to evaluate children’s knowledge, attitudes and praxis about FV, with Cronbach’s> 0.7.	Students should finish the questionnaires in the classroom in the presence of the trained outcome assessors, who can provide guidance and help.
**Questions and recommendations on the implementation of the interventions**		√		Interview questions included school climate and barriers to implementation of interventions, perceived benefits and challenges to intervention, opinions and perceptions about the intervention’s effects on student involvement, behaviorand class-related outcomes, beliefs about parental involvement, potential for sustainability, overall recommendations to other school principals and ideas for improvements.	The questionnaires should be filled by the trained investigators after face-to-face interviews with school principals, teachers and volunteers.

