### 2.8. Outcome Evaluation

The outcome indicator measure will be administered at three points in time. Firstly, a baseline measurement will be taken prior to randomization to a group of six public primary schools. Then the same measurement will be taken after the completion of the six-month intervention, and a final identical measurement will be taken six months after the completion of the formal intervention period to assess the sustainability of the intervention (6 months after completion of the formal intervention period, as recommended by the National Obesity Observatory). Data collection will be completed by trained data collection workers using paper questionnaires, exercise bracelets, height boards, scales and tape measures for students, and electronic questionnaires and interview guides for parents using those already entered into Questionnaire Star. The specific measurement information is shown in Table 2.

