#### 2.9.2. Secondary Outcome

The children’ FV preferences, identification and the attitude and willingness to eat FV.PA frequency and attitudes of children.Daily sedentary time, video screen time and sleep time (unit: minutes).Parental attitudes towards children’s FV intake and SP.Children’s height, weight and waistline.Questions and recommendations on the implementation of the interventions.

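### As Table 2 is written, the secondary outcome on parental attitudes is answered by students, on a questionnaire described as measuring children

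*Protocol article*

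**What the plan says.** Section 2.9.2 of the protocol article includes among the secondary outcomes "Parental attitudes towards children’s FV intake and SP". The construct is an attitude, the people holding it are parents, and it has two objects: FV intake and SP.

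Table 2, under Dietary behavior, has a row with the same label, ticked at baseline and at 6 months. Its instrument cell describes a questionnaire adapted from a KAP (knowledge, attitude and praxis) form, with the purpose "to evaluate children’s knowledge, attitudes and praxis about FV". Its method cell reads "Students should finish the questionnaires in the classroom in the presence of the trained outcome assessors, who can provide guidance and help".

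Section 2.8 describes data collection in general. For parents it plans "electronic questionnaires and interview guides for parents using those already entered into Questionnaire Star". It does not say what these forms contain, and it closes with "The specific measurement information is shown in Table 2".

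**The concern.** The label of the Table 2 row and the content of its cells describe different measurements. The label concerns parents; the instrument cell and the method cell both concern children. Table 2 is where the article fixes who is asked what, so field staff who follow it would give this form to pupils.

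At stake is the meaning of one listed outcome. Children's knowledge, attitudes and practice about FV would be analysed and published as parental attitudes. The row has only two time points. If the baseline is taken from the wrong respondent, it cannot be recovered once the intervention has started, and no change from baseline in parents could then be estimated.

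**Working it through.** No arithmetic applies. The check compares the outcome as defined with its row in Table 2, and then looks for any other place where the outcome could be measured.

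**Step 1: the outcome against its own row.**

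| Element | Section 2.9.2 | Table 2 row |
|---|---|---|
| Whose attitude | Parents | Children (instrument cell) |
| Who answers | Not stated; parents are implied | Students, in class (method cell) |
| Attitude to FV | Yes | Yes, but children's |
| Attitude to SP | Yes | In the row label only; absent from the instrument description |

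The respondent and the construct conflict, in two separate cells. On SP there is no stated conflict; the description is silent.

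**Step 2: the other questionnaire and interview rows of Table 2.**

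| Row | Who answers | Parental attitude? |
|---|---|---|
| CCPAQ, activity frequency and attitudes | Students | No |
| CCPAQ, screen time | Students | No |
| FFQ, FV intake and food frequency | Parents or caregivers | No, intake only |
| DEBQ-C, FV preferences and attitudes | Students | No |
| KAP, labelled parental attitudes | Students | No, as described |
| Implementation interviews | Principals, teachers, volunteers | No |

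One of the six rows is answered by parents: the food frequency questionnaire, where "The questionnaires should be self-reported by parents or other primary caregivers of the students". It records intake. The interview row is completed "after face-to-face interviews with school principals, teachers and volunteers", so parents are not interviewed under it. No row collects an attitude from a parent.

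**Step 3: can Section 2.8 supply the measure?** It shows that a route to parents exists. It names no attitude instrument, however, and it sends the reader to Table 2, where the row in question has students answering. The parent-completed food frequency questionnaire could by itself account for the electronic parent form. Section 2.8 therefore does not resolve the conflict; it adds a third place that does not agree with the other two.

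**The case against.** The strongest reply is that Table 2 may not list everything asked of parents. Section 2.8 mentions parent interview guides, and no row of Table 2 accounts for them. A reader might infer from Table 2 that no parental attitude will be measured at all. The documents do not support that: the content of the parent forms and guides is not given, and attitudes could be among it. What can be said is that no measurement of parental attitudes is specified and that the one row bearing the name specifies something else.

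The method cell may also be a slip. Its sentence recurs word for word in three other rows, which fits text copied down the table or a merged cell expanded in conversion. That weakens any claim that students are the intended respondents. It does not explain the instrument cell, which has its own wording and independently names children.

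A reader might further infer that attitudes to SP will go unmeasured. The adapted items are not shown, and an article need not show them. Only the silence of the description is established.

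Nor does it follow that the caregiver side of the programme could not be evaluated. Section 2.7 records caregivers' attendance and their satisfaction, and the interviews with school staff and volunteers ask about parental involvement. These do not replace an attitude score, but they cover part of the ground, and the article states no analysis that tests a pathway through parental attitudes.

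Finally, an article condenses a fuller protocol. That would excuse missing detail. Here the respondent and the target population are stated, and they contradict the outcome list.

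**Conclusion.** The point stands as an internal inconsistency. Sections 2.8 and 2.9.2 and the Table 2 row do not agree on who answers or on what is measured. Data collected as Table 2 states would be children's answers carrying the name of parental attitudes.

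The size is limited to one secondary outcome. Section 2.10 does not name it among the dependent variables of the GEE models. It plays no part in the sample size in Section 2.3 or in the cost-effectiveness analysis in Section 2.11, and neither primary outcome depends on it.

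The conclusion rests on taking Table 2 at its word, as Section 2.8 directs. If the full protocol routes a parental attitude form to caregivers, the error lies in the published table alone. It should be corrected in either case, because the article as it stands gives the outcome the wrong source.

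**What to change.** Reconcile Sections 2.8 and 2.9.2 and the Table 2 row before baseline data are collected.

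- If parental attitudes are intended: in Table 2, name the parent or primary caregiver as respondent, with delivery through the electronic parent questionnaire of Section 2.8. Name or describe an instrument on parental attitudes that covers both FV intake and SP. The documents contain no such items, so they have to be chosen or written.
- If the children's KAP is intended: list it in Section 2.9.2 as a separate child outcome under its own name, and do not report it as parental attitudes.
- If both are wanted: give each its own row, respondent and instrument.

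It would also help to say in Section 2.8 what the parent interview guides cover, since Table 2 has no row for them.

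The cost is one corrected table row, some items added to a form already planned, and a slight extra burden on caregivers. Sample size, randomisation and the primary analysis do not change.

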## Data Availability

Not applicable.
